### 11.1. Aims

The proposed project will aim to investigate the ability of a virtual reality game (VRG)-based educational intervention to enhance primary schoolchildren’s compliance with hygiene practices and increase their participation in SARS-CoV-2 screening, to prevent SARS-CoV-2 transmission in the community. The objectives are as follows.

To assess the ability of a VRG-based educational intervention to enhance the knowledge and hygiene-practice compliance of primary schoolchildren in terms of the prevention of SARS-CoV-2 transmission, in comparison with a control group receiving usual community care, at 6 months after the intervention.To compare the bacterial loads on primary schoolchildren’s hands between the study group and the control group at 6 months after the intervention.To compare the detection rates of SARS-CoV-2 and other respiratory viruses in primary schoolchildren’s throat gargle samples between the study group and the control group at 6 months after the intervention.To compare the number of schoolchildren who participate in the community SARS-CoV-2 screening programme between the study group and the control group at 6 months after the intervention.

### 11.2. Plan of Investigation

This will be a single-blinded, cluster RCT with two-armed repeated measures.

#### 11.2.1. Subjects

Primary schoolchildren will be recruited from local primary schools. The eligibility criteria will be (1) primary school children aged 6–12, and (2) able to communicate in Chinese and to read Chinese. The exclusion criteria will be (1) reported mental or physical health disorders and (2) engagement in other health educational programmes related to hygiene practices 2 months or less before recruitment. The school management staff will help us to liaise with the schoolchildren and refer them to the research team. Informed consent will be obtained from school principals, parents and schoolchildren before the study begins. To minimise selection bias, the children will not be informed of whether they will join the intervention group or the control group. Potential subjects will be screened and recruited in these schools by the research team. In order to avoid data contamination in the control group, school children who have siblings in the intervention group will not be recruited. Details of the study will be provided to the schools, the schoolchildren and their parents. Sample size has been computed to obtain a statistical power of no less than 0.8 to detect the significance of the four objectives with continuous outcomes at a 0.05 level of significance. With 0.2 as the Cohen’s d effect size and under balanced allocations, we have set the intra-cluster correlation to 0.05, the correlation among level-2 units nested in a cluster to 0.01, the number of level-1 units to 30, and the sample size of level-2 stratified units to 2, we have 18 school clusters in each arm. Therefore, the sample size should be 2160.

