##### Phase 2: Main Study (40 Months)

Intervention group: Educational intervention using a VRG over 3 weeks.

The schoolchildren in the intervention group will take part in an innovative VRG-based educational programme featuring: (1) Web-based health education on (i) SARS-CoV-2 transmission, (ii) proper hand and respiratory hygiene practices and (iii) the importance of community SARS-CoV-2 screening and throat-gargle collection procedures; (2) built-in instant feedback on their performance of hygiene practices; and (3) a chat function for efficient nurse–parent–schoolchild interactivity and communication. The schoolchildren will receive three sessions (one per week) of the VRG-based educational programme, which will be provided by the research team during extracurricular activity time. Each session will consist of two VRGs and will last 30–45 min. Six VRGs will be designed, representing six ascending levels. After completing each level, schoolchildren will be granted access to the next level. This design will engage the schoolchildren in playing the VRGs. Levels 1 and 2 will address the fundamentals of SARS-CoV-2 transmission and hand hygiene; levels 3 and 4 will consist of family-based scenarios exemplifying the chain of infection and throat gargle collection; and levels 5 and 6 will address how to combat germs in school-based scenarios and the importance of community SARS-CoV-2 screening. The schoolchildren will be required to complete electronic questionnaires pre-post and 3 months and 6 months after they participate in the educational programme. Parents will use the online checklist provided to assess schoolchildren’s performance on the return-demonstration of hand hygiene and throat gargle pre–post, and 3 months and 6 months after the educational programme. To ensure the accuracy of the recordings of the schoolchildren’s hygiene practices, the return-demonstration will be video-recorded and uploaded to the online platform by parents, for analysis by the research team.

Control group. The schoolchildren in this group will receive the usual health education or care available in the community. The VRG equipment will not be made available to the schoolchildren in this group within the intervention period.

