#### 11.2.3. Study Design

The duration of each schoolchild’s involvement in the study will be 6 months, with assessments at baseline before the intervention (T1), immediately after the intervention (T2), at 3 months after the intervention (T3), and at 6 months after the intervention (T4). It is proposed that 12 schools will participate in the study every 12 months, and thus it will take 36 months to complete the intervention in 36 schools. Four months will be used for data cleaning, analysis and report writing. Data will be collected at four time-points, T1, T2, T3 and T4, to test the sustained intervention effect.

Randomisation: A large-scale stratified cluster RCT will be undertaken. Primary schoolchildren will be recruited via local conventional school clusters from 18 districts in Hong Kong, which have been chosen to provide a geographically representative sample. The cluster sizes will be equal across school clusters. We will select 36 primary schools and will randomly assign them to the intervention group or the control group in a ratio of 1:1. To adjust for age as a confounding factor, the schoolchildren from each school cluster will be separately drawn from lower grades (Primary 1 to 3) and higher grades (Primary 4–6). Therefore, we have designed a three-level hierarchical mixed model that is randomised at the third level. Here, a school is considered to be a level-3 cluster, the grades within a school are considered to be level-2 stratified units and the schoolchildren in our trials are considered as level-1 units [58].

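### Study 5's sibling exclusion is one-sided and defined by allocation, so eligibility differs by arm; the bias is of unknown, probably small size and can be avoided cheaply

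*Protocol article*

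**What the plan says.** Study 5 randomises schools, not children: "We will select 36 primary schools and will randomly assign them to the intervention group or the control group in a ratio of 1:1" (11.2.3 Study Design). Schools enter in stages: "It is proposed that 12 schools will participate in the study every 12 months" (same section).

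The sibling rule is in 11.2.1 Subjects: "In order to avoid data contamination in the control group, school children who have siblings in the intervention group will not be recruited". It is not one of the formal criteria, which the same section gives as follows: "The exclusion criteria will be (1) reported mental or physical health disorders and (2) engagement in other health educational programmes related to hygiene practices" (the second carries a two-month window).

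On who recruits, 11.2.1 says: "Potential subjects will be screened and recruited in these schools by the research team". The same team runs the game sessions, "which will be provided by the research team during extracurricular activity time" (Phase 2: Main Study). The only protection described is: "To minimise selection bias, the children will not be informed of whether they will join the intervention group or the control group" (11.2.1). Section 11.2 calls the trial single-blinded without saying more. The article does not say that recruiters are unaware of the allocation, or that pupils are enrolled before their school is allocated.

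**The concern.** An eligibility rule in a randomised trial should select the same kind of participant in both arms. This one refers to the arm of the child's sibling and works in one direction only, so following it as written gives arms drawn by different rules. Applying it also brings the allocation into recruitment, where cluster trials are most exposed to selection.

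Family structure could plausibly relate to hygiene habits and respiratory virus detection, both of which feed the primary outcomes in 11.2.5. An intention-to-treat analysis compares the children who were enrolled; it cannot bring back children who were kept out of one arm.

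**Working it through.** **1. Does eligibility differ by arm?** The sentence can be read in two ways.

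| Reading | Who is excluded | Who is kept |
|---|---|---|
| Control schools only (as the purpose clause suggests) | Control-school child with a sibling in an intervention school | Intervention-school child with a sibling in a control school |
| All schools (literal) | Also the second sibling within one intervention school | Both siblings within one control school |

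The second reading can arise in practice because each school supplies pupils from Primary 1 to 3 and from Primary 4 to 6 (11.2.3). Eligibility differs by arm on both readings. The first thins the control arm. The second also thins the intervention arm. The direction of any bias therefore cannot be fixed in advance.

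**2. Can the rule be applied without the allocation?** Take siblings at two schools of the same wave.
- If schools are allocated before pupils are screened, the screener must know which school is an intervention school.
- If pupils are screened first, the rule can operate only by removing pupils once the allocation is known, which is a post-randomisation exclusion.

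Keeping children unaware of their group closes neither route.

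**3. The plan's sample size, and the standard error it implies.** Inputs from 11.2.1: d = 0.2, 30 children per grade stratum, 2 strata per school, correlations 0.05 and 0.01, 18 schools per arm. The power statement is "a statistical power of no less than 0.8 to detect the significance of the four objectives with continuous outcomes at a 0.05 level of significance"; two-sided testing is assumed.
- Design effect = 1 + 30 × (2 − 1) × 0.01 + (30 − 1) × 0.05 = 1 + 0.30 + 1.45 = 2.75.
- Schools per arm = 2 × 2.75 × (1.960 + 0.842)² / (60 × 0.2²) = 17.99, rounded up to 18.
- Total = 36 × 60 = 2160, as stated; power 0.800.
- SE of the arm difference = √(2 × 2.75 / 1080) = 0.0714 SD.

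**4. How large could the direct bias be?** The documents give neither input, so both are assumptions. Let q be the share of otherwise eligible control pupils excluded, and g the difference in SD between excluded and retained pupils. For a comparison of levels, bias = q × g.
- q = 1%, g = 0.1: 0.001 SD, 0.5% of d; type I error 0.050.
- q = 1%, g = 0.5: 0.005 SD, 2.5% of d; type I error 0.0506.
- To reach one tenth of d (0.02 SD), q × g must equal 0.02, for example q = 10% with g = 0.2; type I error is then 0.059.

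**5. What those values of q would require.** Each arm has 18 × 60 = 1080 children.
- q = 1%: 1080 / 0.99 ≈ 1091 screened, about 11 excluded.
- q = 10%: 1080 / 0.90 = 1200 screened, 120 excluded. If each came from a different family, 120 / 1080 = 11% of enrolled intervention children would need a sibling who is otherwise eligible at a control school.

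With 36 schools drawn from 18 districts (36 / 18 = 2 per district if spread evenly), the lower figure looks nearer the mark, but the documents do not settle it.

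**The case against.** **The one-sidedness has a reason.** Contamination runs from intervention to control, so a mirror exclusion protects nothing further. The aim is legitimate. But a symmetric rule meets it equally well without making eligibility depend on arm.

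**The analysis offsets part of the bias.** Section 11.2.5 compares changes from baseline, and the outcomes are measured at T1, before the intervention. A stable difference in level linked to family structure would largely cancel. This stands, with one limit: the objectives in 11.1 are worded as comparisons at 6 months, and differing trends would not cancel.

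**Staggered entry helps in part.** A sibling in an earlier wave's intervention school can be identified without knowing the present school's allocation. On the literal reading such a child is excluded whichever arm the present school is in. This stands for later waves. It does not help within a wave, or on the control-only reading.

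**Enrolment order may be set out in the full protocol.** An article commonly leaves such detail out, so its absence is not the finding. The finding is the stated rule, which within a wave uses the allocation whichever order is followed.

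**Stronger readings a reader might infer.** One is that a large share of control pupils would be lost. An excluded share of 20% would mean 1080 / 0.80 = 1350 screened and 270 excluded, so up to 270 / 1080 = 25% of intervention families with another eligible child at a control school; nothing in the documents supports that. Another is that excluded children carry the full difference between children with and without siblings. The rule removes only those whose sibling is in the intervention group; other children with siblings remain in both arms, so the relevant contrast is probably smaller. A third is that recruiters would select pupils by arm more widely. The text leaves that possible but does not show it.

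**Conclusion.** The point holds as an avoidable selection risk. As written, the rule makes eligibility differ by arm, and within a wave it needs the allocation at recruitment or a removal after allocation. The described safeguard covers only the children.

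Size and direction are unknown. The direct bias is probably small, on two assumptions: few siblings attend different participating schools, and excluded children differ modestly from those retained. The documents do not support calling the trial's comparison seriously biased. The rule should nevertheless be changed before recruitment, because selection at entry cannot be undone in the analysis and the remedy is cheap.

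**What to change.** Replace the sentence in 11.2.1 with a symmetric rule that does not use the allocation, for example:

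> In every school, pupils are screened and consented before that school's allocation is revealed to the recruiting staff. A child with a sibling already enrolled in, or attending, another participating school, in whichever arm, is not enrolled.

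List this among the exclusion criteria, and report the number of sibling exclusions by arm. Siblings within one school may both stay, since they pose no contamination between arms. A scheme that picks one sibling at random across all participating schools would not be practical, because schools enter over 36 months and a later sibling may not be screened until years after the first.

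Cost: a few more pupils excluded, in both arms; household checks against other participating schools, including those of earlier waves; and recruitment of each wave before its allocation is revealed. The target of 60 pupils per school and the total of 2160 do not change.

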To assess intervention effectiveness, campaign registrants will provide basic demographic information (i.e., age, sex, household characteristics, employment status, social media account, contact information) during registration (T0) and complete self-reported measures of their (a) stay-at-home motivation, intention and past-week behaviour; (b) threat and coping appraisals, measured using adapted instruments deployed in recent studies that tested PMT in the COVID-19 context [53,54]; and (c) depressive, anxiety and stress symptoms, as measured using the 21-item Depression Anxiety Stress Scale [57]. Follow-up data will be collected at the end of the active campaign (T1), and every 6 months thereafter until the end of the intervention (T2, T3, T4, T5). Invitations to complete the surveys will be delivered via the participants’ social media accounts, phone calls or email, based on the contact information provided at registration. Up to five attempts will be made before the participant is deemed lost to follow-up for that time point. To assess effectiveness, logic checking and missing data analysis will be performed. Missing data will be handled based on the degree and mechanism of missingness (i.e., deletion or imputation). Generalised estimating equations will be used to model within-subject longitudinal data to estimate population-average changes in stay-at-home motivation, intention and past-week behaviour; COVID-19 threat appraisal; stay-at-home coping appraisal; and psychological well-being (depression, anxiety, stress) across respondents over time. A minimum sample of 515 campaign registrants will be targeted to achieve 80% power and alpha of 0.0042 (to keep the overall type 1 error at 0.05 for 12 outcomes) with small intervention effect (Cohen’s d = 0.2) across timepoints for 6 repeat measures with an assumption of a first order autoregressive covariance pattern and a base correlation of 0.30.

## 10. Study 4

AI-driven Vaccine Communicator: The impact of a Web-based psychoeducation programme with a motivational AI-based digital assistant on COVID-19 vaccine hesitancy in Hong Kong’s population

To address the widespread hesitancy among HK residents toward COVID-19 vaccines, we will develop a Web-based psychoeducation programme, ‘AI-driven Vaccine Communicator,’ driven by artificial intelligence (AI) techniques based on the Vaccine Hesitancy Determinants Matrix Model and MI communication skills and concepts (theoretical underpinnings) [19].

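### Study 5 claims at least 0.8 power for four continuous objectives, but two are binary, and 2160 children give 0.80 for the continuous ones only with no loss to follow-up

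*Protocol article*

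**What the plan says.** The Study 5 sample-size paragraph (Section 11.2.1) claims "a statistical power of no less than 0.8 to detect the significance of the four objectives with continuous outcomes" "at a 0.05 level of significance". It takes "0.2 as the Cohen’s d effect size", and "we have set the intra-cluster correlation to 0.05". It adds a correlation of 0.01 between the two grade strata of a school and 30 children per stratum. The result is 18 schools per arm and 2160 children. Section 11.2.3 says the investigators will "randomly assign them to the intervention group or the control group in a ratio of 1:1".

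Section 11.1 lists four objectives, each assessed 6 months after the intervention:

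1. Knowledge and hygiene compliance.
2. Bacterial load on the hands.
3. "To compare the detection rates of SARS-CoV-2 and other respiratory viruses" in gargle samples.
4. "To compare the number of schoolchildren who participate in the community SARS-CoV-2 screening programme".

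Section 11.2.4 records screening participation as a number and a percentage. Section 11.2.5 names knowledge and practice, bacterial loads and virus detection rates as primary outcomes. It examines all of them by linear mixed-effect modelling, with repeated-measures analysis of covariance among the listed techniques. Screening participation is not in that primary list.

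Study 5 states no attrition allowance. Study 2 (Section 8.2.1) allows 30% and Study 4 (Section 10.2.3) allows 20%.

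**The concern.** The power statement covers all four objectives and calls their outcomes continuous. There are exactly four objectives, so the phrase cannot mean a continuous subset. Virus detection and screening participation are each yes or no per child. For such an outcome a standardised mean difference of 0.2 fixes no difference in rates until a control rate is given, and none is. The claim therefore has no stated basis for half the objectives, one of which concerns a primary outcome.

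Separately, the total is the bare product 2 × 18 × 2 × 30 = 2160. The figure is worded as a floor, but it holds only if all recruited children contribute data at the last assessment.

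What is at stake is how a null result would be read. Someone relying on Section 11.2.1 would take a non-significant difference in virus detection as coming from a comparison with at least 0.8 power. The document does not show that.

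**Working it through.** **Inputs (Sections 11.2.1 and 11.2.3).** Alpha 0.05, taken as two-sided because that reproduces the plan's figure; power 0.80; d = 0.2; allocation 1:1; correlation within a grade stratum ρ1 = 0.05; correlation between strata of a school ρ2 = 0.01; n1 = 30 children per stratum; n2 = 2 strata per school.

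**Reproducing 2160.**
- Unclustered n per arm = 2(1.96 + 0.842)²/0.2² = 392.4.
- Design effect = 1 + (n1 − 1)ρ1 + n1(n2 − 1)ρ2 = 1 + 29 × 0.05 + 30 × 0.01 = 2.75.
- Clustered n per arm = 392.4 × 2.75 = 1079.2; divided by 60 children per school this is 17.99, so 18 schools.
- Total = 2 × 18 × 60 = 2160, an exact match.
- Effective n per arm = 1080/2.75 = 392.7. Power = Φ(0.2 × √(392.7/2) − 1.96) = 0.8003.

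**Continuous outcomes with loss.** The loss rates are assumptions for Study 5; 20% and 30% are those of Studies 4 and 2. Loss reduces n1, which also reduces the design effect.

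| Loss | n1 | Design effect | Power |
|---|---|---|---|
| 0% | 30 | 2.75 | 0.800 |
| 1% | 29.7 | 2.73 | 0.799 |
| 10% | 27 | 2.57 | 0.785 |
| 20% | 24 | 2.39 | 0.767 |
| 30% | 21 | 2.21 | 0.744 |

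For example, at 20% loss: 18 × 2 × 24 = 864 per arm; 864/2.39 = 361.5; 0.2 × √(361.5/2) − 1.96 = 0.729; Φ = 0.767.

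**Why d = 0.2 does not carry over to a rate.** The nearest analogue is Cohen's h = 2 arcsin√p1 − 2 arcsin√p2. A reduction of h = 0.2 means 50% to 40.1%, 20% to 12.7%, 5% to 1.6%, or 2% to 0.2%. The same standardised number runs from a ten-point fall to near-elimination, depending on the control rate.

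**Binary outcomes.** These use effective n = 392.7 per arm, no loss, and the plan's correlations assumed to hold unchanged. The control rates are assumptions. The test is a two-sided comparison of proportions, with pooled variance under the null. For 5% against 2.5%: null standard error √(2 × 0.0375 × 0.9625/392.7) = 0.01356; alternative standard error √((0.0475 + 0.024375)/392.7) = 0.01353; (0.025 − 1.96 × 0.01356)/0.01353 = −0.116; power 0.45.

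| Control rate | Power to detect a halving | Detectable at 0.80: fall / rise (points) |
|---|---|---|
| 50% | above 0.99 | 9.9 / 9.9 |
| 20% | 0.98 | 7.4 / 8.6 |
| 10% | 0.76 | 5.2 / 6.8 |
| 5% | 0.45 | 3.5 / 5.3 |
| 2% | 0.21 | not tabulated |

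**The case against.** The best defence is that the arithmetic is right. The stated inputs give 2160, and for complete continuous data the power is 0.80. That stands: this is not a calculation error.

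The effect of loss is also modest, about 3 points at 20%, and the plan's formula is a post-only comparison that gives no credit for baseline. Section 11.2.5 already plans to compare changes from baseline and lists analysis of covariance. If the correlation with baseline were 0.3 (an assumption), the variance factor would be 1 − 0.09 = 0.91. At 20% loss, 361.5/0.91 = 397.3 and power returns to about 0.80. This also stands. The sample-size statement does not invoke it, however, and the analysis section lists analysis of covariance only as one of several options.

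A reader might infer that the trial is underpowered for infection. The documents do not support that. They give no detection rate, and Section 11.2.4 tests a panel of respiratory viruses, so the rate need not be low. At 10% or 20% the power for a halving is 0.76 or 0.98. The figures also assume that the correlations carry over. With illustrative values of 0.02 and 0.005, the design effect is 1 + 29 × 0.02 + 30 × 0.005 = 1.73, and power for halving 5% rises from 0.45 to 0.64. The supportable statement is that power is unstated and depends on the control rate.

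A reader might extend the point to Study 3, where "A minimum sample of 515 campaign registrants will be targeted to achieve 80% power" also carries no stated loss allowance. A simple paired contrast between two time points needs about 480 rather than 515, so it does not reproduce that plan's calculation and cannot show its power under loss.

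Finally, one might say that an article leaves such detail to a fuller document. That would excuse silence. Here the article makes a positive statement that misdescribes two of its objectives.

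**Conclusion.** The point holds as a misstatement of what the Study 5 sample size supports. Two of the four objectives are binary, and a power of at least 0.8 has no stated basis for them. For the continuous outcomes, 0.80 is the value with no loss rather than a floor: on the plan's normal approximation without baseline adjustment it is about 0.77 at 20% loss and 0.74 at 30%. For the binary outcomes, power to detect a halving runs from about 0.98 (control rate 20%) to 0.21 (control rate 2%), assuming the same correlations and no loss.

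The stated total is not wrong, and nothing here shows that 36 schools are too few. Nor does the defect require moving any outcome to secondary status. A t reference distribution on 34 degrees of freedom would lower the continuous figures further (0.777 with no loss), but the conclusion does not rest on it.

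**What to change.** - **Power statement (Section 11.2.1).** Limit it to the continuous objectives. State power as 0.80 with complete data and about 0.74 to 0.77 with 20% to 30% loss, before any baseline adjustment.
- **Binary objectives.** Give the detectable difference over a range of assumed control rates, labelled as assumptions: for example about 10 points from 50%, and 7 to 9 points from 20%.
- **Analysis (Section 11.2.5).** Analyse virus detection and screening participation with a mixed logistic model that has school and grade-stratum effects, reported with confidence intervals.
- **Baseline.** Commit to adjusting each continuous outcome for its T1 value, which is already collected.

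The cost is a less favourable stated figure and a changed analysis sentence, with no additional schools. For comparison, holding 0.80 without adjustment by recruiting more schools would take 20 per arm (2400 children) at 20% loss or 21 per arm (2520) at 30%; this is not proposed.
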